### Imaging analysis workflow

CT and MRI datasets will be anonymized and transferred to a dedicated research workstation for postprocessing. Tumor and renal parenchyma segmentations will be performed semi-automatically by an imaging engineer and a radiologist with expertise in genitourinary imaging, blinded to histopathological results and elastography measurements. Segmentations will include the whole tumor volume on axial images. An in-board software (Sophia DDM for Radiomics, SophiaGenetics SA, Saint-Sulpice, Switzerland) was used.

For renal parenchyma analyses, cortical and medullary ROIs will be separately defined on anatomically matched slices.

Multimodal image co-registration between CT and MRI datasets will be performed using rigid registration followed, when necessary, by deformable registration to compensate for respiratory and positional differences. All images will be resampled to a common voxel resolution before voxel-wise analysis.

Quality control procedures will include visual assessment of registration accuracy and exclusion of non-diagnostic datasets.

### Statistical analysis

Imaging data will be acquired across multiple modalities, including MRE (μMRE), US-E, and CT (dCT, dCT40s, dCT90s, dCT10min), alongside clinical and morphological variables such as BMI, sarcopenia, lesion size, volume, location, histological type, malignancy status, and histological grade for clear cell renal carcinoma, where applicable. Quantitative variables will be extracted and analyzed for each region of interest (ROI). Descriptive statistics will summarize categorical variables as frequencies and percentages, while continuous variables will be presented as mean, standard deviation, median, range, and interquartile range.

The primary objective is to develop a regression model to predict μMRE based on CT-derived density values. The dataset will be divided into a 70% training set and a 30% test set, and various regression algorithms (linear regression, elastic net, k-nearest neighbors, support vector machines, random forests, and artificial neural networks) will be compared using repeated nested cross-validation. Model performance will be evaluated based on coefficient of determination (R²), mean squared error (MSE), and root mean squared error (RMSE), with RMSE serving as the primary criterion for model selection. Reproducibility of MRE measurements will be assessed through repeated acquisitions, with the highest-quality sequence selected for model development.

Secondary analyses will investigate the interrelationships between biomechanical parameters across imaging modalities. Spearman’s rank correlation coefficient will be used to assess correlations between elasticity values from MRE, US-E, and CT densities. The feasibility and image quality of DWI will be evaluated using a five-point qualitative scale, contrast-to-noise ratio, signal-to-noise ratio, and systematic reporting of artifacts. Non-diagnostic examinations and potential limiting factors—such as patient morphotype, sarcopenia, and lesion characteristics—will be documented. The repeatability of elastography measurements will be quantified using intraclass correlation coefficients and Bland-Altman plots. Cases of modality de-correlation will be explored through paired scatterplots and descriptive analysis of discordant data points.

The final statistical analysis plan will be reviewed and approved by the Scientific Committee prior to database lock.

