**Methods and analysis:**

This monocentric, prospective, exploratory, non-randomized, and non-blinded diagnostic study will enroll 50 adults undergoing partial or radical nephrectomy for renal tumors at the University Hospital of Bordeaux. All participants will undergo a predefined multimodal imaging protocol—including contrast-enhanced CT, multiparametric magnetic resonance imaging (MRI) with -MRE and US-E—conducted between inclusion and the day before surgery. The primary objective is to construct a regression model predicting MRE-derived elasticity (μMRE) from CT density values using multiple machine-learning algorithms evaluated through repeated nested cross-validation. Secondary analyses will include voxel-level and region-of-interest correlations across modalities, feasibility and image-quality assessment of DWI-vMRE, repeatability of elastography measurements, identification of limiting factors such as BMI, sarcopenia, lesion location and architecture, evaluation of inter-modality de-correlation and associations with final histopathology (including subtype and grade).

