### Study population

The study will enroll 50 patients with renal tumors referred for surgical management at the University Hospital of Bordeaux. Patients eligible for inclusion must be at least 18 years old or older, scheduled for nephrectomy for renal neoplasm within the Urology Department, and have a planned or available multiphasic CT as part of their preoperative workup. Participants must also provide informed consent for inclusion in the UroCCR cohort and participation in the Rein-3D Print Mechanics study, with the condition that they are affiliated with social security system. Exclusion criteria include pregnancy or breastfeeding, contraindications to MRI or gadolinium-based contrast agents, previous renal biopsy <15 days before MRI, and certain comorbidities such as obesity (body mass index (BMI) ≥ 30 kg/m²), thoracolumbar spinal fixation, or the presence of small (<2 cm) cystic or necrotic renal tumors with a solid component. Additionally, patients with ascites, legal protection measures, or difficulty in understanding and expressing themselves in French will be excluded.

All study data will be recorded in the imaging systems (Carestream PACS; Philips) and UroCCR database, managed by the CREDIM (Centre de Recherche et Développement en Informatique Médicale) at the University Hospital of Bordeaux. The database is authorized by the French Data Protection Authority (CNIL; authorization DR-2013–206, request n°912578) and operates under the national MR-001. The study involves senior urologists, expertised radiologists from the uro-vascular imaging department, the reference pathologist, biomedical engineers, data managers and biostatisticians.

Data entry was performed by trained personnel, and clinical variables were coded using standard dictionaries (MedDRA, ATC). Data quality was ensured through automated checks and query resolution. All data were pseudonymized, securely stored, and transferred via a protected platform when required. Confidentiality was maintained in accordance with regulatory standards, and study data were archived for 20 years.

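### The protocol pairs a 70/30 split with repeated nested cross-validation and does not say which gives the reported R² and RMSE; a patient-level hold-out would rest on about 15 patients

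*Protocol article*

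**What the plan says.** Enrolment is fixed in Study population: "The study will enroll 50 patients with renal tumors referred for surgical management".

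The Statistical analysis section then sets two schemes in one sentence, which provides for a "70% training set and a 30% test set, and various regression algorithms". The split is the first scheme. In the second, the six methods, which range from linear regression and elastic net to random forests and neural networks, "will be compared using repeated nested cross-validation". The performance measures follow: R², MSE and RMSE, "with RMSE serving as the primary criterion for model selection". It does not say whether these come from the test set or from the outer folds.

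The abstract (Methods and analysis) describes the primary model as built "using multiple machine-learning algorithms evaluated through repeated nested cross-validation" and does not mention a hold-out.

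The unit of the split is not given. The Statistical analysis section says "Quantitative variables will be extracted and analyzed for each region of interest (ROI"), while Study setting puts the CT and MRI analysis at voxel level. Imaging analysis workflow defines whole-tumour, cortical and medullary regions, and removes non-diagnostic datasets from the analysis.

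**The concern.** Both schemes can supply an out-of-sample performance figure for the same primary model, and they may disagree. With 50 patients the choice between them matters. A single 30% hold-out scores few patients and depends on one random draw, whereas outer-fold predictions can score every evaluable patient.

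The precision of the main result is therefore at stake. So is its definition: if both figures exist and neither is named as primary beforehand, the choice can be made after both have been seen. A split below patient level would bring a different problem, optimism rather than imprecision.

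**Working it through.** **Inputs.** From the protocol: 50 patients, a 70/30 split, six algorithms, and RMSE as the selection criterion. The article gives no derivation or precision target for 50, so there is no planned figure to reproduce. Assumed: a true R² of 0.3, 0.5 or 0.7, normal errors and, at first, one independent unit per patient.

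**1. Test-set size, if the split is by patient.** 0.30 × 50 = 15 test and 0.70 × 50 = 35 training patients. With an assumed 10% non-diagnostic loss, 45 remain and 0.30 × 45 = 13.5, so 13 or 14 test patients.

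**2. Interval for R².** Fisher z on r = √R², with standard error 1/√(n − 3). For R² = 0.5, r = 0.707 and z = 0.881.
- n = 15: 0.881 ± 1.96/√12 = 0.316 to 1.447. Back-transformed and squared, this is 0.09 to 0.80 (width 0.71).
- n = 50: 0.881 ± 1.96/√47 = 0.596 to 1.167, giving 0.29 to 0.68 (width 0.39).

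**3. Interval for RMSE.** With n·MSE/σ² distributed as chi-square on n degrees of freedom, the limits are the estimate times √(n/χ²) at the 97.5% and 2.5% quantiles.

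| Patients scored | RMSE factor | R² interval, true 0.3 | true 0.5 | true 0.7 |
|---|---|---|---|---|
| 15 | 0.74–1.55 | 0.00–0.69 | 0.09–0.80 | 0.32–0.89 |
| 35 | 0.81–1.30 | 0.07–0.56 | 0.24–0.71 | 0.49–0.84 |
| 50 | 0.84–1.24 | 0.10–0.51 | 0.29–0.68 | 0.53–0.82 |

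The RMSE factors for 15 and 50 correspond to −26% to +55% and −16% to +24%.

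**4. Check by simulation.** Steps 2 and 3 treat out-of-fold errors as independent, which is only approximate. A simulation avoids that assumption. It used a linear model with four CT predictors and compared one random 35/15 split with 5-fold cross-validation repeated five times on all 50 (2,000 runs per setting).
- Standard deviation of estimated R², hold-out against cross-validation: 0.36 against 0.14 (true R² 0.3), 0.33 against 0.13 (0.5), 0.22 against 0.09 (0.7).
- Standard deviation of RMSE at R² 0.5: 0.141 against 0.080, a ratio of 0.141/0.080 ≈ 1.8.
- Central 95% of estimated R² at true R² 0.5: −0.43 to 0.73 against 0.15 to 0.62.

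**5. Several regions per patient.** With three regions per patient and an assumed within-patient error correlation of 0.5 (true R² 0.5, 1,500 runs), the standard deviation of R² is 0.13 against 0.07. Both are smaller, but the hold-out still has about twice the spread.

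**6. The possible readings side by side.**
- Split by patient, hold-out is the headline: about 15 patients carry the result.
- Split by patient, nested cross-validation only in the training set and taken as the headline: the estimate rests on 35, and 15 are still set aside.
- Nested cross-validation on all 50: the split adds nothing, and the test patients have already helped to choose the algorithm.
- Split by region or voxel: there are many more test rows, but the same patient can fall in both sets, so performance is optimistic.

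**The case against.** The strongest defence is that nested cross-validation within the training set, followed by one check on an untouched test set, is a conventional two-stage design and no contradiction. The abstract may simply be condensed. The hold-out would also have a purpose: if the best of six algorithms is picked on its outer-fold RMSE, that RMSE is optimistic, and fresh patients correct for it. The study is exploratory, and which figure is the headline, how folds are grouped and whether the model is refitted are details that an article may leave to the analysis plan.

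Much of this stands, and it rules out stronger readings that a reader might infer:
- That the primary estimate definitely rests on 15 patients. No section says so, and the abstract points towards nested cross-validation.
- That the 0.09 to 0.80 interval is the one to expect. It assumes one unit per patient, whereas the workflow defines several regions.
- That the final model is trained on 30% fewer patients. This holds only if there is no refit, on which the text is silent.
- That the result could not tell a useful model from a useless one. The protocol sets no threshold for usefulness, and at an assumed R² of 0.5 even the 15-patient Fisher interval excludes zero.

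Two parts of the defence fail. The split is not a detail left open: it is a stated choice for the primary objective, and every reading in the working has a cost or makes it redundant. The optimism from picking a winner can be removed by choosing the algorithm inside the inner loop, without giving up any patients.

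**Conclusion.** The point holds in conditional form. The protocol fixes a 70/30 split beside repeated nested cross-validation and leaves open both the source of the reported R² and RMSE and the unit of the split.

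If the hold-out is by patient and is the headline, the width of the R² interval rises from 0.39 to 0.71 at an assumed R² of 0.5. In simulation the standard deviation of R² is 2 to 2.6 times as large, and that of RMSE about 1.8 times. These sizes rest on assumed R² values, normal errors, a linear model and an assumed within-patient correlation. The direction does not change across the settings tried. This is an avoidable loss and an ambiguity worth removing; it does not invalidate the study.

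**What to change.** In the Statistical analysis section and the analysis plan:

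1. Replace the 70/30 split with repeated nested cross-validation on all evaluable patients, with folds grouped so that all regions and voxels of a patient stay together.
2. Treat the choice among the six algorithms as a tuning decision, made by RMSE inside the inner loop.
3. Name the outer-loop R² and RMSE, with a patient-level interval such as a patient bootstrap, as the single primary performance result.
4. Refit the selected procedure on all evaluable patients to obtain the final model.

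The cost is wording and computing time, with no change to recruitment or imaging. The final analysis plan is due for approval before database lock, so the change can be made there. The drawback is that no separate test set remains, so the report must say that external validation is still needed. That would also be true after testing on about 15 patients from the same centre.

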### Study setting

This study aims to investigate the relationships between renal tumor biomechanical properties measured by multimodal imaging and underlying tumor characteristics, with the broader objective of improving non‑invasive diagnostic approaches. The study will enroll 50 patients scheduled for nephrectomy over an 18‑month period, with follow‑up extending 4 months after inclusion. To date, 40 patients have been enrolled, and recruitment is expected to be completed by September 2026. Approximately 250 patients per year are referred to the Department of Urology for the initial evaluation of renal lesions, establishing a robust recruitment base that is further strengthened by their established clinical and research collaborations through multidisciplinary tumor board meetings. Eligible patients will be recruited during urology consultations at Pellegrin Hospital or after identification by radiologists during imaging sessions. All participants will provide written informed consent in accordance with the approved protocol. Preoperative imaging will include ultrasound elastography, mpMRI (including MRE), and contrast‑enhanced CT, all performed within a standardized preoperative window to ensure methodological consistency. These imaging procedures will take place at Saint‑André Hospital for MRI and at Pellegrin Hospital for ultrasound examinations, using standardized equipment and performed by senior radiologists, with routine care multiphasic CT incorporated as clinically indicated. After the nephrectomy pathological analyses will follow standard institutional workflows. Imaging data will be analyzed at the voxel level for MRI and CT, and at the region of interest (ROI) level for US-E. All data will be managed securely according to protocol specifications until completion following the availability of the final histopathological report.

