### Outcome measures

The primary outcome of this study is to develop a predictive model of biomechanical properties of both normal and pathological renal tissue, using MRE as the reference, based on density values from multiphasic CT. All analyses will be conducted before the definitive histological diagnosis.

The secondary outcomes are:

Multimodal correlation: to correlate elasticity values obtained by MRE, and ultrasound elastography with CT density values, on a voxel to voxel, ROI to ROI, and anatomical region basis across all CT acquisition phases.Feasibility of DWI-vMRE: This study aims to assess the feasibility and optimization of parameters for DWI-vMRE using a clinical 1.5-Tesla MRI scanner. It will focus on evaluating key performance metrics, including image quality (qualitative assessment), contrast-to-noise ratio (CNR), signal-to-noise ratio (SNR), and the identification and documentation of artifacts.Feasibility of elastography modalities: to assess the feasibility of MRE, and US–E for quantifying renal parenchymal and tumoral stiffness, and to identify limiting factors (e.g., BMI, sarcopenia, lesion location, size, and architecture), including enumeration of non-diagnostic examinations.Repeatability analysis: to evaluate the repeatability of MRE, and US-E across the cohort and within subgroups defined by patient morphotype and tumor characteristics, using intraclass correlation coefficients and Bland–Altman plots.De-correlation and bias analysis: to identify situations of de-correlation or potential biases between biomechanical measurements obtained from MRE and US-E (e.g., extreme elasticity values, morphotype-related limitations).Histopathological associations: to assess associations between biomechanical properties (measured or CT-predicted) and final histological subtype; and, for clear cell renal cell carcinoma, with histological grade. This includes ROC curve analyses and identification of potential diagnostic cutoff values.

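### Plain Spearman is the only method named for an outcome that includes voxel-level MRE-CT correlation, although voxels are nested in tissues within 50 patients

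*Protocol article*

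**What the plan says.** Outcome measures in the protocol article defines the first secondary outcome as multimodal correlation: "to correlate elasticity values obtained by MRE, and ultrasound elastography with CT density values, on a voxel to voxel, ROI to ROI" and by anatomical region, for every CT phase. MRE and US-E stand together in that sentence, so read literally the voxel basis covers both.

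The Statistical analysis section gives one method for this outcome, Spearman's "rank correlation coefficient will be used to assess correlations between elasticity values from MRE, US-E, and CT densities". It names no per-patient summary and no repeated-measures or clustered version. It also names no confidence interval, test or significance level for these correlations. It says that quantitative variables are extracted and analysed per ROI, and that a final statistical analysis plan will be approved before database lock.

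Three other sections bear on the point:

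- **Study setting** assigns a unit to each modality: "Imaging data will be analyzed at the voxel level for MRI and CT, and at the region of interest (ROI) level for US-E".
- **Imaging analysis workflow** prepares the voxel-level data for CT and MRI: "Multimodal image co-registration between CT and MRI datasets will be performed using rigid registration", and "All images will be resampled to a common voxel resolution before voxel-wise analysis". It segments the tumour and defines cortical and medullary ROIs separately.
- **Study population** gives the number of independent units: "The study will enroll 50 patients with renal tumors referred for surgical management".

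**The concern.** The unit named in the outcome and the method named in the statistics section do not fit each other. Voxels from one tumour or one kidney share a patient, a scanner session, a contrast injection and a tissue type. Two problems would follow if they were put into one Spearman coefficient.

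The first is what the coefficient means. A pooled value combines three associations: between patients, between tissues, and between voxels of the same tissue. A CT-based stiffness map, the aim stated in the Abstract, needs to know whether denser voxels are stiffer within a tissue. A pooled value could be sizeable merely because tumour differs from parenchyma in both density and stiffness.

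The second is precision. The usual standard error of a correlation counts every pair as independent. Based on the voxel count, it would be far too small for data from 50 patients, and weak or absent associations would look firmly established.

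A smaller matter is that Outcome measures lists US-E under the voxel basis, while Study setting places it at ROI level.

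**Working it through.** The article gives no figure to reproduce here: no target correlation, precision, alpha or power accompanies the 50 patients. The calculations show what pooling would do; they do not describe an analysis that the article sets out.

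**Inputs from the article:** 50 patients; several tissues per patient (tumour, cortex, medulla).

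**Assumptions, because the article gives neither value:** m = 100 or 1,000 voxels per patient (3 for the ROI level); intraclass correlation (ICC) within patient of 0.1 to 0.5, equal in both modalities.

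**1. Apparent precision.** Fisher z interval with SE = √(1.06/(n − 3)), at a coefficient of 0.30, where atanh(0.30) = 0.310.

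- n = 50 (one value per patient): SE = √(1.06/47) = 0.150; 95% CI 0.015 to 0.540.
- n = 50 × 1,000 = 50,000 (voxels counted as independent): SE = √(1.06/49,997) = 0.0046; 95% CI 0.292 to 0.308.

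This shows only how strongly the interval depends on the unit that is counted.

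**2. Understatement of the SE with no true association.** The variance of the pooled coefficient is inflated by about 1 + (m − 1) × ICC_x × ICC_y. With equal ICCs this is 1 + (m − 1) × ICC², and the SE is understated by its square root. For m = 1,000 and ICC 0.3: 1 + 999 × 0.09 = 90.91, and √90.91 = 9.5.

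The formula was checked with 1,000 simulated null data sets per setting, using 50 patients and patient random effects in both variables:

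| m per patient | ICC | SE ratio, formula | SE ratio, simulated | Rejections at nominal 5% |
|---|---|---|---|---|
| 1,000 | 0 | 1.0 | 0.98 | 4.6% |
| 1,000 | 0.1 | 3.3 | 3.0 | 52% |
| 1,000 | 0.3 | 9.5 | 8.8 | 84% |
| 1,000 | 0.5 | 15.8 | 15.1 | 92% |
| 100 | 0.1 | 1.4 | 1.35 | 14% |
| 100 | 0.3 | 3.1 | 3.1 | 55% |
| 3 (ROIs) | 0.1 | 1.0 | 0.96 | 4% |
| 3 (ROIs) | 0.3 | 1.1 | 1.1 | 7% |
| 3 (ROIs) | 0.5 | 1.2 | 1.2 | 10% |

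The precision problem therefore belongs to the voxel level. It vanishes if the ICC is zero and is small with about 3 ROIs per patient.

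**3. Meaning of the pooled coefficient, with no inference involved.** Take two tissues in equal shares, with no association within either, whose means differ by d within-tissue SDs in both density and stiffness (d is an assumption). The pooled Spearman coefficient is then 3 × (Φ(d/√2) − 0.5)²:

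- d = 1: 3 × (0.760 − 0.5)² = 0.20
- d = 1.5: 3 × (0.856 − 0.5)² = 0.38
- d = 2: 3 × (0.921 − 0.5)² = 0.53

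Simulation gave nearly the same pooled values, with within-tissue coefficients near 0. A pooled 0.5 is thus compatible with no voxel-level relation inside any tissue.

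**4. US-E.** Outcome measures attaches the voxel basis to MRE and US-E jointly. Study setting gives US-E the ROI level, and Imaging analysis workflow describes co-registration for CT and MRI only. Together they show that a voxel-level US-E comparison is not planned, and that the outcome sentence is worded too broadly.

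**The case against.** The strongest reply is that the article never describes the faulty analysis. It does not say that voxels are pooled over patients, and it plans no p-value or interval for these correlations. Independence is needed for the usual standard error, not for calculating the coefficient. Spearman within each patient is still Spearman, so the stated wording permits the better analysis. The statistics section speaks of analysis per ROI, where the effect is small. The imaging section already separates tumour, cortex and medulla, and the outcome includes an anatomical region basis. The study is exploratory, the outcome is secondary, and a statistical analysis plan that is not shown may settle the unit.

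Much of this stands. A reader might infer that the plan treats thousands of voxels as independent and will report error bars that are too narrow. The article supports neither part: pooling and error bars are not stated, and voxel counts are not given. A reader might also infer that voxel matching is impossible for US-E. The text shows only that it is not planned. Nor is between-tissue association irrelevant, since the primary outcome covers both normal and diseased tissue.

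What remains is that the article fixes a voxel basis and names a single method that takes no account of nesting. The absence of planned tests does not dispose of this, because a pooled coefficient can mislead on its own (step 3 of the working). Defining separate tissue ROIs does not by itself say that voxel-level coefficients will be calculated separately by tissue and patient.

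**Conclusion.** The concern holds as a mismatch between a named unit and a named method, with the handling of nesting left open. It does not hold as a finding that the plan commits to pooled voxel inference.

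If voxels were pooled, the naive SE would be too small by about 1.4-fold (100 voxels per patient, ICC 0.1) to about 15-fold (1,000 voxels, ICC 0.5), and about 9-fold at 1,000 voxels and ICC 0.3. Each of these sizes rests on assumed voxel counts and ICCs. The possible distortion of the coefficient itself depends on how far the tissues differ, which is also unknown. The US-E point is a wording conflict between two sections. Severity is moderate, for a secondary outcome in an exploratory study.

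**What to change.** In the final statistical analysis plan, and in the outcome wording where it can still be amended:

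1. For each CT phase, compute the voxel-level MRE-CT Spearman coefficient within each patient and tissue (tumour, cortex, medulla). Summarise these over patients, for example as a mean on the Fisher z scale, with a 95% interval from a bootstrap that resamples patients.
2. At ROI or region level, respect patient clustering wherever an interval or test is reported, for example with a mixed model or repeated-measures correlation with patient as the cluster.
3. If a pooled coefficient over tissues is also shown, label it as a mixture of between- and within-tissue association and attach no interval or p-value based on the voxel count.
4. Name the unit for each modality pair and align Outcome measures with Study setting: voxel, ROI and region level for MRE with CT; ROI or region level only for any comparison with US-E.

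No new data are needed. The cost is revised wording, slightly more analysis, and wider intervals than a voxel count would give.

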## Materials and methods

### Aim

The following protocol tries to evaluate the concordance of advanced imaging techniques in assessing renal tissue stiffness for preoperative evaluation of renal tumors in patients undergoing a partial or radical nephrectomy for renal tumor at the Centre Hospitalier Universitaire Bordeaux. This protocol includes multiphasic CT, MRE and US-E, performed between inclusion and the day before surgery.

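### The MRE versus US-E bias outcome is given no statistic that measures bias between the two modalities

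*Protocol article*

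**What the plan says.** The Aim section of the protocol article says that the protocol tries to "evaluate the concordance of advanced imaging techniques in assessing renal tissue stiffness", and names multiphasic CT, MRE and US-E as the techniques. Among six secondary outcomes, Outcome measures includes one on de-correlation and bias, which is "to identify situations of de-correlation or potential biases between biomechanical measurements obtained from MRE and US-E". Its examples are extreme elasticity values and limits set by body type.

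The Statistical analysis section gives two methods for comparing modalities:

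- "Spearman’s rank correlation coefficient will be used to assess correlations between elasticity values from MRE, US-E, and CT densities"
- "Cases of modality de-correlation will be explored through paired scatterplots and descriptive analysis of discordant data points"

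Methods that measure agreement appear once in that section, for a different outcome: "The repeatability of elastography measurements will be quantified using intraclass correlation coefficients and Bland-Altman plots". Outcome measures ties them to repeatability in the same way.

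The primary objective is separate: "The primary objective is to develop a regression model to predict μMRE based on CT-derived density values", with RMSE as the criterion for choosing the model. The section ends by saying that the final analysis plan will be approved before database lock.

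**The concern.** An outcome about bias between two measurements of stiffness calls for an analysis on the scale of the measurements: how far apart they are on average, how widely the differences scatter, and whether the gap changes with stiffness. The article's own example of extreme elasticity values raises the last of these.

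The only inter-modality statistic named works on ranks. It has the same value whether US-E reads equal to MRE, two units higher, or three times as high. The accompanying scatterplots leave the size of any bias to the eye. The article does not say what makes a point discordant, and no limits of agreement are planned that could supply a yardstick.

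If the methods are carried out as written, the bias outcome will end in a picture and a rank correlation. A reader could not learn by how much MRE and US-E differ in cortex, medulla or tumor, or how precisely that is known.

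**Working it through.** The plan gives no figure to reproduce on this point. Two things can be checked: whether the named statistic responds to bias, and whether an agreement analysis would be precise enough at the planned size.

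**1. Response to bias.** Assumed inputs, none from the documents: true stiffness with mean 5 and SD 1.5, independent measurement error with SD 0.5 in each modality, 50 pairs, 2000 simulated sets. MRE is m and US-E is u, with u left unbiased, shifted by +2, or multiplied by 1.5 or 3.

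| Scenario | Spearman | Lin's concordance | Mean difference | 95% limits of agreement | Points above identity line |
|---|---|---|---|---|---|
| No bias | 0.881 | 0.895 | 0.00 | −1.38 to 1.38 | 49.8% |
| +2 | 0.881 | 0.491 | 2.00 | 0.62 to 3.38 | 99.8% |
| ×1.5 | 0.881 | 0.462 | 2.50 | 0.21 to 4.78 | 98.3% |
| ×3 | 0.881 | 0.106 | 9.99 | 3.37 to 16.61 | 99.8% |

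The mean differences and concordance values can be checked by hand.

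- Variance of an unbiased reading = 1.5² + 0.5² = 2.5; covariance of m and the unbiased u = 1.5² = 2.25.
- Mean difference: 2; 0.5 × 5 = 2.5; 2 × 5 = 10.
- Lin's coefficient = 2·cov / (var m + var u + squared mean difference):
  - no bias: 4.5/5 = 0.90
  - +2: 4.5/(5 + 4) = 0.50
  - ×1.5: 6.75/(2.5 + 5.625 + 6.25) = 0.47
  - ×3: 13.5/(2.5 + 22.5 + 100) = 0.108

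These agree with the simulated averages to within 0.01. Spearman is identical in every row because adding a constant or multiplying by a positive factor leaves ranks unchanged. The last column shows that a scatterplot with an identity line is not blind to bias, provided both axes use one scale.

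**2. Constant or proportional.** The slope of difference on mean is [(var u − var m)/2] / [(var u + var m + 2·cov)/4].

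- No bias and +2: numerator 0, so slope 0.
- ×1.5: 1.5625/3.71875 = 0.42.
- ×3: 10/9.625 = 1.04.

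This regression therefore separates a fixed offset from one that grows with stiffness. Unequal measurement error in the two modalities also tilts the slope. The planned repeatability analysis gives the error SDs needed to judge that.

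**3. Precision.** One pair per patient; half-widths of 95% CIs in units of the SD of the differences. Mean bias: t/√n. Each limit: t·√(1/n + 1.96²/(2(n−1))). The planned enrolment is 50 (Study population). The values 40 and 30 are assumptions, made because non-diagnostic examinations are expected and will be counted.

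| Usable pairs | t | Mean bias | Each limit |
|---|---|---|---|
| 50 | 2.010 | 0.28 | 0.49 |
| 40 | 2.023 | 0.32 | 0.55 |
| 30 | 2.045 | 0.37 | 0.65 |

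For n = 50: √(0.0200 + 0.0392) = 0.243, and 2.010 × 0.243 = 0.49.

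**The case against.** The best defence is that the outcome is exploratory case-finding: in whom, and where, do the two modalities part company? Scatterplots and a description of odd points, alongside the documented body type and lesion features, suit that purpose. The per-modality means and medians in the descriptive statistics would also reveal a gross offset on a common scale. This stands as far as it goes. Large bias could be seen; it would not be measured, and its dependence on stiffness would not be estimated.

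A second defence is that the full analysis plan is not shown and may fill the gap. That covers details such as the common scale, the handling of several ROIs per patient and the definition of discordance. It does not cover the main point, because the article is not silent. It states the methods for this outcome, and it assigns Bland-Altman to a different one.

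A reader might go further and infer that the study's aim is agreement between MRE and US-E, that this aim will fail, and that the plan is unable to detect bias at all. The documents do not support that. The concordance in the Aim section also covers CT, whose density values are not a stiffness measure and cannot have limits of agreement with one. Nowhere does the article claim that MRE and US-E are interchangeable. Rank correlation is a reasonable choice for the separate multimodal correlation outcome.

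The threefold scenario should not be read as a forecast either. A factor of that kind could be a mere difference in the modulus reported. The article does not say whether the two modalities share a scale.

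**Conclusion.** The mismatch is real and narrow. One secondary outcome concerns bias between MRE and US-E, and no between-modality agreement statistic is named for it. Spearman's coefficient carries no information on constant or proportional bias. That is a mathematical property and does not depend on the simulated values; only the concordance values, differences and limits in the example do. The scatterplots can show a gross offset but do not quantify bias, its spread or its trend with stiffness.

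The consequence is an outcome left unquantified, in a study that calls itself exploratory. It deserves correction because it is cheap to correct. The precision figures assume one pair per patient and roughly normal differences with constant spread.

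**What to change.** State in the analysis plan, for the MRE versus US-E outcome:

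- the common stiffness scale on which both modalities are expressed, with any conversion and its assumptions;
- Bland-Altman analysis of paired ROI-level values, separately by tissue, giving the mean difference and 95% limits of agreement with confidence intervals that allow for several ROIs per patient;
- the regression of difference on mean, to show whether the gap changes with stiffness;
- discordant points defined as those outside the limits. Under normality about 5% fall outside by construction (0.05 × 50 = 2.5 of 50 pairs), so this selects cases to describe and is not a test.

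If no common scale can be defended, use an errors-in-variables regression such as Deming, with the error-variance ratio taken from the repeatability data, or Passing-Bablok. Keep Spearman as a descriptive measure and for comparisons with CT density.

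The cost is plan wording and a little more analysis on data already being collected. Study setting reports 40 of 50 patients enrolled and the plan is to be approved before database lock, so the analysis can still be specified in advance. The price is modest precision, especially if many examinations are non-diagnostic, and the intervals should be reported so that readers can see it.
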